## Abstract

**Introduction:**

Adolescent mental health problems represent a significant global health issue, particularly in low- and middle-income countries, such as the Republic of North Macedonia and the Republic of Moldova. Effective and scalable interventions are urgently needed to address these challenges.

**Methods and analysis:**

This protocol outlines a multicountry cluster randomised factorial trial, implemented according to the multiphase optimisation strategy (Phase 2), which evaluates the effectiveness and costs of three add-on components for the Parenting for Lifelong Health for Parents and Teens programme: adolescent mental health tools based on UNICEFs Helping Adolescents Thrive comics, adolescent peer support based on UNICEFs ‘I Support My Friends’ intervention and engagement booster designed to enhance attendance and programme completion through incentives. The study will recruit 720 families and involve 64 clusters in North Macedonia and Moldova. Primary outcomes will include adolescent internalising problems and social support, family functioning and attendance during the programme. Secondary outcomes will assess broader aspects of mental health among caregivers and adolescents, as well as implementation and cost outcomes. Data will be collected at baseline and postintervention, approximately, 8 weeks later. Statistical analyses will include regression models to assess the main and interaction effects of the intervention components and cost analyses.

**Ethics and dissemination:**

The study received ethical approval from the University of Klagenfurt in Austria (approval number: 2023–013), the Medical Faculty at St. Cyril and Methodius University in North Macedonia (approval number: 03-2144/4) and the National Committee of Ethical Expertise for Clinical Trials in Moldova (approval number: 1476). The results will be disseminated through peer-reviewed journals, conferences, webinars in multiple languages, regional forums, stakeholder meetings with policymakers and practitioners, public communication through media engagement and open access platforms, including data sharing and early release of findings.

**Trial registration details:**

Trial registration: NCT06562244; Project page: https://www.flourish-study.org/about.html

Strengths and limitations of this studyThe study employs a multicountry cluster randomised factorial trial, according to the optimisation phase of the multiphase optimisation strategy framework, which allows for a thorough evaluation of add-on intervention components and their interaction effects on primary outcomes, such as adolescent internalising symptoms, social support, family functioning and programme attendance, as well as secondary outcomes related to broader mental health impacts on caregivers and adolescents.The intervention has been carefully adapted to the local contexts of North Macedonia and Moldova, ensuring cultural relevance and increasing the likelihood of successful implementation and participant engagement.The intervention is designed to prioritise scalability (eg, brief, easy to disseminate, no licensing cost for materials and small engagement boosters), which facilitates broader implementation and sustainability in low- and middle-income countries.While participants and assessors are initially blinded to group assignments and assessors are blinded at postassessment, complete blinding of participants and facilitators is not maintained throughout the study due to the psychosocial nature of the intervention.

## Introduction

 Adolescent mental health is a critical global concern, with estimates indicating that approximately one in seven teenagers worldwide presents psychological problems.^1^ Furthermore, research indicates that one-thirds of individuals experience their first mental disorder before the age of 14, increasing the risk of future mental disorders in adulthood.^2 3^ Poor mental health during adolescence is associated with long-term negative outcomes, such as lower educational attainment, poor physical health and reduced quality of life.^4 5^ The economic impact of untreated adolescent mental health issues is significant, leading to higher costs for healthcare and social services.^6^

In low- and middle-income countries (LMICs), such as the Republic of North Macedonia and the Republic of Moldova (henceforth, North Macedonia and Moldova), adolescents face additional developmental challenges due to heightened socioeconomic stressors, adverse childhood experiences and limited access to mental health services.^7 8^ Moreover, containment measures of the COVID-19 pandemic have placed additional stress on adolescents and their families, leading to increased abuse and neglect.^9^ North Macedonia and Moldova have also experienced an influx of refugees due to the war in Ukraine, many of whom are parents with children facing unique challenges, such as processing of war-related experiences, displacement and challenges related to integrating into new communities.^10 11^

Target 3 of the 2030 UN Agenda for Sustainable Development Goals aims to ensure healthy lives and well-being for all age groups, emphasising the necessity of programmes that promote adolescent mental health, especially in LMICs.^12^ Parenting interventions are recommended as critical strategies to strengthen adolescent–caregiver relationships, enhance parenting styles and improve interpersonal and emotion regulation skills.^13^ One such suite of programmes is the ‘Parenting for Lifelong Health’ (PLH), developed in collaboration with UNICEF, WHO and other international agencies and researchers. These are group-based behavioural programmes that focus on enhancing psychosocial skills and family relationships, targeting different age groups.^14^ The PLH for Young Children, targeting caregivers of children aged 2–9, has been successfully implemented across various cultural settings (Foran *et al* and Heinrichs *et al*).^15^,^17^ Furthermore, the PLH for Parents and Teens programme has been tested in South Africa, supporting its potential for broader applications among adolescents.^18 19^

The systematic optimisation of family programmes is crucial to enhance scalability and sustainability in low-resource settings.^20^ The multiphase optimisation strategy (MOST) provides a critical framework for optimising and evaluating complex behavioural interventions and consists of three phases.^21 22^ The preparation phase (Phase 1) involves developing a conceptual model for the intervention and pilot testing. The optimisation phase (Phase 2) uses methods, such as factorial designs, to test different combinations of intervention components to identify the most effective and efficient configuration. Finally, the evaluation phase (Phase 3) involves conducting a randomised controlled trial (RCT) to assess the optimised intervention’s effectiveness. Using the MOST framework, previous research in Eastern Europe found PLH for Young Children to improve parenting behaviours and child mental health (Foran *et al* and Heinrichs *et al*).^16^ Building on this research, the ‘family-focused adolescent and lifelong health promotion’ (FLOURISH) project aims to adapt, optimise and evaluate an intervention package based on the PLH for Parents and Teens programme targeting adolescents aged 10–14 years and their caregivers in North Macedonia and Moldova. This intervention package seeks to enhance adolescent mental health and well-being by developing skills in both teens and caregivers. Phase 1 of the FLOURISH project aimed to assess the feasibility and preliminary efficacy of the adapted PLH programme.^23^ Alongside local contextual adaptations to the PLH for Parents and Teens programme, the intervention incorporated three additional components to improve programme participation, retention rates and effectiveness. These components included adolescent mental health tools based on UNICEFs Helping Adolescents Thrive (HAT) comics, adolescent peer support based on UNICEFs ‘I Support My Friends’ intervention and engagement boosters. The inclusion of these components is critical for several reasons. First, the HAT framework provides structured tools that can help adolescents manage stress and develop essential emotion regulation skills.^24^ Second, peer support can enhance adolescents’ sense of belonging and reduce social isolation, promoting better mental health outcomes through community and relational support.^25^ Finally, the engagement booster is essential for ensuring high participation and retention rates in the programme, thereby maximising the intervention’s overall impact.^26^ Although these three components are considered crucial, their effectiveness and cost-effectiveness remain uncertain, highlighting the need for thorough evaluations. Engagement boosters were found to increase the attendance of caregivers participating in the PLH for Young Children programme in three Eastern European countries (Foran *et al*), suggesting this component may also be relevant for adolescents and their caregivers’ engagement in the PLH for Parents and Teens programme.

This article presents the Phase 2 protocol of FLOURISH, which focuses on the optimisation of the adapted PLH programme by assessing the effectiveness and costs of HAT, adolescent peer support and the engagement boosters, as well as their combinations. By selecting the add-on components and combinations that prove most cost-effective, the PLH for Parents and Teens programme can be improved and more easily scaled up to maximise its impact on adolescent mental health, facilitating long-term delivery and sustainability in North Macedonia and Moldova. The optimal combination of add-on components in Phase 2 will be tested in a multicentre RCT in Phase 3.

The study is characterised by the following research questions.

What is the efficacy of each add-on component on primary and secondary outcomes?What is the efficacy of the add-on components on implementation outcomes?What are the costs of programme delivery and components?What are the efficacy and cost consequences of the different combinations of components and what is the optimal combination to be tested in a multicentre RCT in Phase 3?How is the programme implemented and received?

## Methods

### Study design

This study employs a multicountry cluster randomised factorial trial, according to the optimisation phase of the MOST framework. The study has been preregistered in clinical trials registry (NCT06562244) and follows the Consolidated Standards of Reporting Trials (CONSORT) guidelines.^27^ The standard protocol items: recommendations for interventional trials checklist is included as a supplementary document (online supplemental appendix 1).^28^

### Study setting

The study will be implemented in North Macedonia and Moldova and it is supported by two health networks: the Institute for Marriage, Family and Systemic Practice (ALTERNATIVA) in North Macedonia and the Health for Youth Association (HYA) in Moldova. ALTERNATIVA comprises a network of psychologists, social workers and family therapists. HYA supports publicly funded youth clinics that deliver preventive and therapeutic services, addressing areas, such as sexual and reproductive wellness, psychological well-being, substance misuse and prevention of violence. Both health networks have experience in delivering PLH programmes within the MOST framework (Foran *et al* and Heinrichs *et al*).^16^

### Participants and recruitment

The study will involve primary caregivers and their adolescents aged 10–14 years. For inclusion in the study, caregivers will have to meet the following criteria: they must be at least 18 years old at the baseline assessment, live with the adolescent in a household where the adolescent has slept at least four nights per week in the previous month, be able to speak at least one of the local languages (Romanian or Macedonian) and provide consent for both their own and their adolescent’s participation in the study by signing an informed consent. Adolescents must be between 10 and 14 years old at the baseline assessment, and both the caregiver and the teen must agree to participate in the study. In North Macedonia, adolescents aged≥14 are also required to provide consent in order to comply with local legal and ethical requirements. An example of the informed consent for caregivers and adolescents is included as a supplementary document (online supplemental appendix 2). Exclusion criteria for both caregivers and adolescents include significant psychiatric disorders, acute distress or physical health conditions that could impede their ability to participate in the study. These are assessed through an exclusionary statement as a part of the consent procedures.

All interested families meeting the criteria above will be eligible to participate in the study, with additional efforts made to include more economically and socially vulnerable groups using a proportionate universalism approach. This method focuses on individuals at higher than average risk without the need for preliminary screening.^29^ In North Macedonia, the recruitment process will primarily take place in schools, whereas in Moldova, it will be conducted in youth clinics. Families will be invited via multiple means to join the study (eg, school referrals, clinic referrals and community outreach) and provided an informational document that explains the study’s objectives, intervention specifics, the voluntary nature of involvement, data handling procedures, potential risks and benefits and provides contact details for additional questions or clarifications.

The programme will be implemented by the current staff and established networks of ALTERNATIVA and HYA. This staff includes data assessors, facilitators and supervisors. Data assessors are trained research staff responsible for administering participant assessments, ensuring the accurate data collection. Facilitators are trained professionals with prior experience in parenting interventions, responsible for delivering the intervention, leading sessions and guiding participants through skill-building activities. Supervisors are experienced senior staff who provide oversight and support to facilitators, ensure programme fidelity and conduct facilitator performance evaluations. Facilitators, supervisors and data assessors must be 18 years or older, participate in training, agree to fulfil their respective roles in programme delivery, supervision or assessment and provide consent.

### Intervention

To assess the efficacy and costs of the three add-on components (HAT, adolescent peer support and engagement booster) to the adapted PLH for Parents and Teens programme, the present study will implement a factorial cluster RCT.^22^

#### Intervention core programme: PLH for parents and teens programme

The core programme implemented in the FLOURISH project is PLH for Parents and Teens. In Phase 1 of FLOURISH, the PLH programme followed an adaptation drawing on the PLH manual used in a South African evaluation study and other programme versions.^23^ To support scalability, the PLH programme is condensed into six 2-hour weekly group sessions and delivered to groups of 10–12 adolescent–caregiver pairs. In each weekly session, a new skill relevant to adolescence is introduced and practised. Often, the group is split into parallel adolescent and caregiver sessions to allow open sharing. Home practice tasks are also assigned between sessions to reinforce learning. For example, after a session on building positive relationships, caregivers and adolescents are asked to spend at least 15 min of uninterrupted quality time together each day, during which the adolescent chooses an activity they enjoy. Caregivers are also encouraged to practice structured praise, offering at least one specific, positive comment to their adolescent each day. The programme is delivered by two facilitators per group with weekly supervision to ensure high-quality delivery. Facilitators, supervisors and coordinators complete trainings on the PLH programme and facilitation skills. Supervisors receive additional 2-day training on supervision techniques and on using the PLH facilitators assessment tool (PLH-FAT)^30^ to evaluate the facilitators’ performance in delivering the programme and provide supervision. For Phase 2, the core programme will maintain the same structure, with refinements based on the qualitative feedback, primarily from advisory and focus groups from Phase 1 (eg, less focus on sexuality, changes in the order of the topics as well as pilot feasibility study results; Shenderovich *et al*; Waller and Mueller *et al*). The adapted manual is freely available on the project website (https://www.flourish-study.org/).

#### Component 1: HAT (on/off)

The HAT component,^24^ which operates in an on/off mode (ie, delivered vs not delivered), consists of a group workshop designed to provide adolescents with essential skills using the UNICEFs ‘Magnificent Mei’ comic series and corresponding workbook for teenagers and facilitators.^31^ The workshop is delivered by a facilitator and includes two interactive sessions. Each session lasts for approximately 2 hours and focuses on four out of six selected chapters from the comics. The selected topics from the ‘Magnificent Mei’ comic series are: recognising emotions, dealing with stress, dealing with problems and working out conflict and being there for each other. In ‘recognising emotions’, adolescents learn to identify and express their feelings. ‘Dealing with stress’ teaches them about the effects of stress on the body and calming techniques like breathing exercises. ‘Dealing with problems’ covers conflict resolution and effective communication among friends and family. ‘Working out conflict and being there for each other’ emphasises listening and understanding different perspectives, concluding with a lesson on building strong relationships through mutual support. In Phase 2 of the FLOURISH project, the workshop will be implemented between the third and fifth PLH sessions (weeks 4 and 6).

#### Component 2: adolescent peer support (on/off)

The adolescent peer support component is designed to teach adolescents how to support friends in distress. Based on UNICEFs ‘I Support My Friends’ initiative^32^ and adaptions for the FLOURISH project, the programme consists of a half-day workshop divided into three main parts: look, listen and link. In the ‘look’ part, adolescents learn to identify signs of distress in peers. The ‘listen’ part focuses on developing active listening skills, while the ‘link’ part teaches when and how to seek additional support. As a result, adolescents receiving this component may acquire essential skills to recognise signs of distress in their peers and offer immediate support. They will learn to refer friends to adults for further help, respond appropriately to their friends’ emotional reactions, assist in accessing necessary resources and services and ensure their friends’ safety from further harm. Furthermore, by emphasising the importance of seeking help and support in challenging situations, the programme equips children and adolescents to assist their peers effectively. The workshop targets groups of 10–12 adolescents and will be delivered following the first PLH session (week 2).

#### Component 3: engagement booster (high/low)

We will include and evaluate a specific component designed to motivate families to commit to and complete the PLH programme. This component will consist of two levels of incentives. In the low level, all families receive minimal refreshments at each session. Additionally, all families receive a certificate of attendance if they attend one to four out of six PLH sessions or a certificate of successful completion if they attend five or six sessions. In the low level, all families receive refreshments at each session. In the high-level condition, participants additionally receive vouchers as incentives. Youth receive a voucher (equivalent to €10) for attending five or six sessions, and caregivers receive a voucher (equivalent to €5) for the same level of attendance. Both adolescents and parents can attend the sessions independently of each other, and the incentives are based on their individual attendance. Certificates and vouchers will be distributed during a small closing ceremony at the end of the sixth PLH session (week 7).

Table 1 shows the adapted intervention structure, including the PLH core programme and the three components.

**Table 1 T1:** Adapted intervention structure for phase 2 optimisation study

Week	Session	Core programme	Components		
		PLH for parents and teens*	HAT†	Engagement booster	Adolescent peer support†
1	0	Pregroup session home visits		Refreshments*	
2	1	Developmental stages‡		Refreshments*	Look, listen, link workshop
3	2	Building a positive relationship through spending time together§		Refreshments*	
4	3	Talking about emotions and sensitive topics‡	Recognising emotions and dealing with stress	Refreshments*	
5	4	What do we do when we are angry‡		Refreshments*	
6	5	Establishing rules and routines§	Dealing with problems and working out conflict and being there for each other	Refreshments*	
7	6	Problem solving‡		Refreshments* Certificate of attendance* Certificate of successful completion (five–six PLH sessions)* €10 voucher for adolescents and €5 for caregivers (five–six PLH sessions each)¶	

* Delivered to all families.

† Delivered to adolescents only in specific experimental conditions.

‡ Caregivers and adolescents’ joint and separate session.

§ Caregivers and adolescents’ joint session.

¶ High-level component: only in specific experimental conditions.

HAT, helping adolescents thrive; PLH, parenting for lifelong health.

### Experimental conditions

The factorial experiment will consist of eight conditions (2^3^), stratified by country (table 2).

**Table 2 T2:** Experimental conditions

Condition number	Components		
	HAT	Engagement booster	Adolescent peer support
1	On	High	On
2	On	High	Off
3	On	Low	On
4	On	Low	Off
5	Off	High	On
6	Off	High	Off
7	Off	Low	On
8	Off	Low	Off

Note. On/Off=delivered/not delivered.

HAT, helping adolescents thrive.

### Hypotheses of the study

Figure 1 presents the conceptual model for the current study, including the theory of change regarding the PLH for Parents and Teens programme and the components effects. Each hypothesis is directly connected to specific outcomes, in line with causal models for RCTs of complex interventions.^33^

**Figure 1 F1:**
[figure not shown]
Conceptual model for PLH Teens and add-on components. Notes: ^1^Delivered to adolescents; ^2^Delivered to caregivers; ^3^Reported by adolescents; ^4^ Reported by caregivers. Additional direct paths and interaction effects between components are not included in the figure for simplicity. We hypothesise that caregivers and adolescents across all conditions will benefit from the core PLH programme, resulting in improvements in family communication and positive parenting, as well as a reduction in parental distress. These changes are expected to be associated with enhancements in adolescent mental health and well-being. HAT, helping adolescents thrive; PLH, parenting for lifelong health.

It is hypothesised the following.

Caregivers and adolescents across all conditions will benefit from the adapted core PLH for Parents and Teens programme, resulting in improvements in primary and secondary outcomes (eg, family communication and parenting, as well as a reduction in parental stress). These changes are expected to be associated with improvements in adolescent mental health (direct and indirect effects).Adolescents receiving the HAT component will show better socioemotional skills compared with those not receiving the HAT component. This, in turn, will lead to greater improvements in family functioning (eg, family communication) and adolescent mental health.Caregivers and adolescents participating in the high engagement component will exhibit higher attendance rates in PLH compared with those involved in the low engagement component. This higher rate of participation is anticipated to lead to greater improvements in both primary (eg, adolescent mental health, via indirect effects and social support) and secondary outcomes (eg, family functioning, parenting and parental stress).Adolescents receiving the peer support component will show greater improvements in social support and socioemotional skills compared with those not receiving the peer component. This, in turn, will lead to greater improvements in family functioning and adolescent mental health.

Additional exploratory hypotheses.

There will be a significant interaction between the engagement booster component and the adolescent peer support component. Specifically, when both components are high/on, there will be greater improvements in primary outcomes (eg, adolescent mental health and social support) compared with when either component is low/off. These improvements are expected to occur through indirect effects, such as enhanced socioemotional skills and family communication.The combination of the HAT component and adolescent peer support component will result in significantly greater improvements in both primary (eg, adolescent mental health) and secondary outcomes (eg, family functioning) when both components are on compared with when either component is off (ie, interaction effect). These improvements are expected to occur through indirect effects, such as enhanced socioemotional skills and increased social support.The HAT component and engagement booster component will interact to produce greater improvements in adolescent mental health, participation and socioemotional skills when both components are high/on compared with when either component is low/off.The PLH programme will be implemented with high fidelity and will be well received by participants, with feedback from participants indicating high satisfaction.The programme will have broader cost consequences beyond direct implementation costs, and different component combinations will have different incremental efficacies and costs representing alternative optimisation scenarios in terms of cost-effectiveness.

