### Sample size

A power analysis was conducted to determine the sample size required for this study, using the ‘FactorialPowerPlan’ function within the R-package ‘MOST’.^34^ The study is designed as a factorial experiment with 3 factors and 64 clusters (eight conditions with four groups per condition per country). To detect a small effect with an 80% power and alpha of 0.10 (as recommended for factorial trials in MOST),^35^ considering a small amount of intraclass correlation (ICC) in the absence of intervention (ie, ICC=0.01) and low clustering of change scores (ICC of change scores=0.10), the sample size should include approximately 7 families per cluster, corresponding to 448 families. To consider drop-out after recruitment, it is estimated to recruit approximately 10–12 families per cluster (640–768 families).

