### Data collection and outcomes

Outcomes will be assessed at baseline and postassessment, approximately, 8 weeks later. Data collection from adolescents and caregivers will be conducted primarily using computer-assisted self-report questionnaires on tablets (open-source software platform, Open Data Kit), with data assessors assisting adolescents and caregivers in completing the questionnaires. Adolescents and caregivers will complete assessments separately. Data assessors will receive comprehensive training from the study investigators. This training will cover ethics, informed consent procedures, safety procedures, adverse event reporting and interviewing techniques.

Outcome measures without official translations were adapted and translated following best practice guidelines for cross-cultural adaptation (Piolanti *et al*; Waller and Mueller *et al*).

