### Statistical analysis

Analyses will examine the main effect of each component and interaction effects using regression analyses, with adjustments based on baseline data. For pre- and postassessments, intent-to-treat analyses accounting for clustering and stratification by country will be used. Separate models will be tested using effect coding for treatment effects.^44^

Indirect models based on the hypothesised theory of change will be examined using a Mplus software^45^ or R^46^ and accounting for clustering within groups and using bootstrapping procedures (eg, engagement booster component increasing attendance, which, in turn, is related to greater changes in primary and secondary outcomes). Multigroup analyses or t-tests at baseline will be performed to identify differences between countries and other contextual or demographic variables. Any missing data will be assessed and managed using either multiple imputation or full information maximum likelihood estimation, following the intention-to-treat analysis protocol.^47^

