Ethical approval for this study has been obtained from several bodies: the Institutional Review Board for Research Ethics at the University of Klagenfurt in Austria (approval number: 2023–013), the Ethical Commission for Human Research at the Medical Faculty of St. Cyril and Methodius University in North Macedonia (approval number: 03-2144/4) and the National Committee of Ethical Expertise for Clinical Trials at the Ministry of Health in Moldova (approval number: 1476).

The FLOURISH project is dedicated to sharing its findings with relevant stakeholders to ensure the broadest impact and application of the research and has a dissemination and exploitation plan that was prepared at the onset of the project and updated at regular intervals as a deliverable to the European Commission. Dissemination efforts will be multifaceted, encompassing a variety of strategies to reach a wide audience. These efforts will include organising meetings with key stakeholders, engaging with media outlets and distributing information through scientific publications for researchers and other summaries for various stakeholder groups. The project will leverage the existing networks, the FLOURISH project website and social media outlets to expand its reach and engagement.

The primary focus of dissemination activities will be in North Macedonia and Moldova, the countries where the research is being conducted. However, the project also aims to engage stakeholders across the broader Eastern European region. By working with these diverse partners, the project aims to promote that the research findings are integrated into policy and practice, ultimately improving adolescent mental health and well-being

This factorial study is designed to evaluate the effectiveness and costs of the adapted PLH for Parents and Teens programme and different add-on components, as well as their combination, to provide valuable insights that will inform the design of the subsequent RCT planned as the next phase of the FLOURISH project. This thorough methodology will support the FLOURISH project in creating scalable, evidence-based interventions designed to enhance the mental health and well-being of adolescents and their families in North Macedonia and Moldova.

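### PLH is given in all eight conditions, so hypothesis 1 and the closing aim claim a PLH effect that the randomised design cannot show

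*Protocol article*

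**What the plan says.** Under Hypotheses of the study, the first item, placed ahead of the exploratory hypotheses, reads "Caregivers and adolescents across all conditions will benefit from the adapted core PLH for Parents and Teens programme, resulting in improvements"; it applies this to both the primary and the secondary outcomes. The section introduces its hypotheses as consistent with causal models for RCTs. The last paragraph of Ethics and dissemination says: "This factorial study is designed to evaluate the effectiveness and costs of the adapted PLH for Parents and Teens programme and different add-on components".

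Elsewhere the scope is narrower. The Introduction says that this phase "focuses on the optimisation of the adapted PLH programme by assessing the effectiveness and costs of HAT, adolescent peer support and the engagement boosters". The Abstract, the research questions on efficacy and the opening of the Intervention section also confine efficacy to the add-ons and their combinations. Under Statistical analysis, "Analyses will examine the main effect of each component and interaction effects using regression analyses, with adjustments based on baseline data"; no contrast for PLH is described.

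On delivery, the Table 1 footnote attached to the core programme reads "Delivered to all families". Table 2 crosses three factors only: HAT, engagement booster and adolescent peer support. On timing, "Outcomes will be assessed at baseline and postassessment, approximately, 8 weeks later".

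**The concern.** A trial can estimate by randomisation only what it varies. PLH does not vary here: condition 8 (HAT off, booster low, peer support off) still receives PLH with refreshments and certificates, and no untreated, waitlist or usual-care group is described. Hypothesis 1 and the closing aim therefore promise a conclusion about PLH that the allocation cannot deliver.

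What is at stake is the interpretation of the results. If scores improve between baseline and post-assessment, the first hypothesis could be reported as confirmed and PLH described as effective. The Strengths and limitations list mentions incomplete blinding but not the absence of a comparator without PLH, so a reader is not warned.

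**Working it through.** **1. Is a PLH effect estimable?** Code the three factors as -1/+1. The saturated model for the eight cells has 8 columns (intercept, three main effects, three two-way interactions, one three-way interaction) and rank 8. A PLH column equals 1 in every cell, which is the intercept column. Adding it gives 9 columns and leaves the rank at 8. PLH is completely aliased with the intercept, at any sample size.

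**2. What direct evidence is left?** Change from baseline to about 8 weeks, pooled over conditions. Three features of the plan limit what this change can mean:
- There are two measurement times and no group without PLH, so maturation and retesting are not separable from PLH.
- Participant timeline gives starts in October 2024 and January 2025 in North Macedonia and January 2025 in Moldova. Having all eight conditions in each phase protects the add-on contrasts from season, but not the before-after change.
- CBCL internalising and family functioning are caregiver reports and social support is an adolescent report. Under Randomisation and blinding, participants are not blind after baseline.

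**3. The plan's own sample size.** Inputs from the Sample size section: 8 conditions x 4 groups x 2 countries = 64 clusters, and 64 x 7 = 448 families. This arithmetic is right. The plan's aim there is "To detect a small effect with an 80% power and alpha of 0.10", with no numeric effect size, so the 80% cannot be reproduced. With design effect 1 + (7 - 1) x 0.10 = 1.6, two-sided alpha 0.10 and a noncentral t with 64 - 8 = 56 degrees of freedom, 448 families give 80% power at d = 0.30. That power belongs to an add-on main effect and says nothing about PLH.

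**4. How sensitive would a pooled pre-post test be?** This is an illustration, since the plan specifies no such test. Assumptions: 448 families, 7 per cluster, change-score ICC 0.10, two-sided alpha 0.10 (the plan does not state sidedness), normal approximation, true PLH effect zero.
- SE of mean change = sqrt(1.6 / 448) = 0.0598 SD of change.
- Drift detected with 80% power = (1.645 + 0.842) x 0.0598 = 0.149 SD of change.

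Probability that the test is significant, by size of the background drift:

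| Drift (SD of change) | Probability |
|---|---|
| 0 | 0.10 |
| 0.05 | 0.22 |
| 0.10 | 0.51 |
| 0.15 | 0.81 |
| 0.20 | 0.96 |

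The documents give no size for the drift, so the table shows a range. The result in step 1 does not depend on it.

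**The case against.** The best case for the plan has four parts.

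- *Nothing that the trial decides depends on hypothesis 1.* The research questions on efficacy, the power calculation, the regression models and the selection process all concern components and their combinations. The Introduction already gives the Phase 3 RCT the task of assessing the optimised intervention. This stands, and it keeps the point below a design fault. A reader might infer that the trial needs an arm without PLH or that the add-on comparisons are compromised. Neither follows: holding the core programme constant is legitimate in an optimisation trial, and the add-on contrasts remain randomised.
- *No pooled pre-post test is planned.* Correct. The sensitivity figures are conditional on someone running one. How hypothesis 1 would be summarised may be left to an analysis plan that is not shown. But no analysis plan can supply the missing contrast, so the causal wording remains wrong.
- *There is some randomised information on PLH exposure.* The booster is meant to raise attendance, and indirect models from booster through attendance to outcomes are planned. This stands in part. Such models give at most indirect, dose-type evidence under mediation assumptions, and never a comparison of PLH with none.
- *The context is mild.* Hypothesis 1 accompanies a theory of change, and the closing sentence is a summary that goes on to the design of the next RCT. That is fair, but both still assert benefit or effectiveness of PLH.

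A reader might also infer a predictable regression to the mean from the outreach to vulnerable families. The documents do not support a figure. Under Participants and recruitment, every interested family that meets the criteria is eligible, families are not screened beforehand, and acute distress is an exclusion. Recruiting on social disadvantage is not selection on the baseline score.

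**Conclusion.** The point holds as a mismatch between claim and design. Hypothesis 1 and the effectiveness part of the closing aim cannot be answered by the randomised comparisons, and they conflict with the add-on-only scope of the Abstract, Introduction, Intervention and Statistical analysis sections. This rests only on PLH being constant across the eight conditions, which Tables 1 and 2 show.

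The size of the risk is conditional. If before-after change were tested in the pooled sample under the assumptions above, a drift of about 0.15 SD of change would pass as a benefit about four times in five. Severity is moderate: what the trial may conclude about PLH changes, while what it may conclude about the add-ons does not.

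**What to change.** Two edits:

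- **Hypothesis 1.** Restate it as a descriptive estimate of within-group change from baseline to post-assessment, with confidence intervals that allow for clustering. Use no causal or efficacy wording, and say that the change is uncontrolled.
- **Closing paragraph of Ethics and dissemination.** Limit the effectiveness aim to the three add-on components and their combinations, delivered on top of PLH. The costs of delivering PLH may stay, because programme delivery costs are one of the research questions.

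The cost is a few sentences. Sample size, randomisation, add-on analyses and component selection stay as they are. The trial gives up only a claim that it could not support.
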